# Stereotactic EEG-guided radiofrequency thermocoagulation versus anterior temporal lobectomy for mesial temporal lobe epilepsy with hippocampal sclerosis: study protocol for a randomised controlled trial

**DOI:** 10.1186/s13063-021-05378-3

**Published:** 2021-06-29

**Keywords:** Mesial temporal lobe epilepsy, Stereotatic electroencephalograph (SEEG)-guided radiofrequency thermocoagulation (RF-TC), Randomised controlled trial

## Abstract

**Introduction:**

In this report, we aim to describe the design for the randomised controlled trial of Stereotactic electroencephalogram (EEG)-guided Radiofrequency Thermocoagulation versus Anterior Temporal Lobectomy for Mesial Temporal Lobe Epilepsy with Hippocampal Sclerosis (STARTS). Mesial temporal lobe epilepsy (mTLE) is a classical subtype of temporal lobe epilepsy that often requires surgical intervention. Although anterior temporal lobectomy (ATL) remains the most popular treatment for mTLE, accumulating evidence has indicated that ATL can cause tetartanopia and memory impairments. Stereotactic EEG (SEEG)-guided radiofrequency thermocoagulation (RF-TC) is a non-invasive alternative associated with lower seizure freedom but greater preservation of neurological function. In the present study, we aim to compare the safety and efficacy of SEEG-guided RF-TC and classical ATL in the treatment of mTLE.

**Methods and analysis:**

STARTS is a single-centre, two-arm, randomised controlled, parallel-group clinical trial. The study includes patients with typical mTLE over the age of 14 who have drug-resistant seizures for at least 2 years and have been determined via detailed evaluation to be surgical candidates prior to randomisation. The primary outcome measure is the cognitive function at the 1-year follow-up after treatment. Seizure outcomes, visual field abnormalities after surgery, quality of life, ancillary outcomes, and adverse events will also be evaluated at 1-year follow-up as secondary outcomes.

**Discussion:**

SEEG-guided RF-TC for mTLE remains a controversial seizure outcome but has the advantage for cognitive and visual field protection. This is the first RCT studying cognitive outcomes and treatment results between SEEG-guided RF-TC and standard ATL for mTLE with hippocampal sclerosis. This study may provide higher levels of clinical evidence for the treatment of mTLE.

**Trial registration:**

ClinicalTrials.gov NCT03941613. Registered on May 8, 2019. The STARTS protocol has been registered on the US National Institutes of Health. The status of the STARTS was recruiting and the estimated study completion date was December 31, 2021.

## Background

Drug-resistant epilepsy is defined as regular intake of more than one first-line antiepileptic drug (AED) for more than 2 years without adequate seizure control [1]. Frequent seizures severely impact the quality of life and may also lead to cognitive deterioration. As the most common and best-characterised electro-clinical epilepsy syndrome, mesial temporal lobe epilepsy (mTLE) accounts for approximately 40% of epilepsy cases in adults [2]. TLE refers to syndromes in which the temporal lobe is involved in the generation or conduction of the epileptic network [3, 4]. In patients with mTLE, epileptic activity originates from the mesial structures of the unilateral temporal lobe, including the hippocampus, amygdala, and parahippocampal gyrus. First described in the nineteenth century, hippocampal sclerosis (i.e. neuronal loss and gliosis) is the most common pathology in patients with mTLE [5].

In 1950, Penfield and Flanigin described anterior temporal lobectomy (ATL) for the treatment of temporal lobe seizures [6]. After more than half a century of development, ATL has become the standard treatment for mTLE, achieving nearly 80% seizure freedom in the long term (i.e. after 5 years) [4, 7, 8]. However, ATL is associated with complications such as visual field defects, memory loss, and emotional disturbances, which can decrease the quality of life following the procedure [9, 10]. In addition, approximately 20% of patients experience recurrent seizures to varying degrees, which may be attributable to inaccurate localisation of the epileptogenic zone or incomplete surgical resection [8].

Radiofrequency thermocoagulation (RF-TC) was first utilised for patients with mTLE in 1980 [11]. However, given the limitations of imaging technology and stereotactic techniques at that time, it was associated with lower rates of seizure freedom than ATL [12–14]. Recent advancements in multi-modal imaging technology and the development of frameless, robotic stereotactic assistance systems have dramatically improved RF-TC, which can now be guided by stereotactic electroencephalography (SEEG), helping to localise and target the epileptogenic zone [14–16]. Although thousands of patients have undergone RF-TC, the results of this procedure for mTLE remain controversial.

## Methods/design

### General study design

STARTS is a single-centre, two-arm, randomised controlled, parallel-group clinical trial. The study will enrol patients with refractory mTLE, who will be followed up for 1 year after treatment. Primary outcome measures will include intelligence quotient. Secondary outcome measures will include seizure outcome, visual field, quality of life, average hospitalisation expenses, and adverse events.

### Participant selection

The study aims to enrol male or female participants ranging in age from 14 to 65 years who have had drug-resistant seizures for at least 2 years and who have been determined via detailed evaluation to be candidates for surgery prior to randomisation. Patients will be evaluated based on seizure history and mTLE semiology from outpatient and multidisciplinary team (MDT). Pre-surgical examinations will be carried out before enrolment. The following eligibility criteria have been adopted:
Normalised treatment with at least one or more first-line antiepileptic drugs (AEDs) for more than 2 years with still seizure attack. Appropriate doses must have been administered, and treatment must have failed due to inefficacy rather than intolerancePersistence of disabling seizures (at least three times per 3 months or greater) and at least one or more seizures in the preceding monthAge ≥ 14 years at enrolmentSimple and complex partial seizures, with or without secondary generalised seizures beginning in childhood or later, with or without prior febrile convulsionsAuras occurring in isolation that are not primary sensory in nature (other than olfactory or gustatory)Intelligence quotient (I.Q.) greater than 70Hippocampal atrophy on T1-weighted magnetic resonance imaging (MRI) with increased ipsilateral mesial signal on T2-weighted and Flair MRIInterictal EEG showing focal or lateralised spikes over the temporal, frontal, or sphenoid electrodeIctal EEG onset that is focal or lateralised on the ipsilateral sideIpsilateral temporal focal hypometabolism on positron emission tomography (PET)Consensus of ipsilateral mesial temporal origin based on a multidisciplinary discussionAbility to understand and speak Mandarin

Exclusion criteria are as follows:
A history of serious cerebral insult after the age of 5Progressive neurological disorders or mental retardation (I.Q. < 70)Psychogenic seizuresFocal neurological deficits other than memory disturbancesAny unexplained focal or lateralised neurological deficits other than memory dysfunctionTemporal neocortical or extratemporal lesions on MRIPsychosis, current or recent substance abuse, suicidality, or anorexiaSevere systemic diseaseUnequivocal focal extratemporal EEG slowing or interictal spikesLesions outside of the mesial temporal area on MRIDiffuse unilateral or bilateral hypometabolism on PETContralateral or extratemporal ictal onsetPersistent extratemporal/predominant contralateral focal interictal spikes or slowing; generalised interictal spikesInclusion in any clinical trialPregnancy

### Interventions

All participants will be randomised into two groups: an ATL group (arm 1) and an SEEG-guided RF-TC group (arm 2). The full technological flow of this RCT is shown in Fig. 1.

**Fig. 1 Fig1:**
[figure not shown]
Timeline of the STARTS protocol. Patients assigned to the ATL group will undergo ATL directly. Patients assigned to the RF-TC group will undergo SEEG implantation and monitoring until the first seizure episode. Then, 3D-crossing RF-TC will be conducted

Patients enrolled in arm 1 will undergo open ATL following pre-surgical evaluation, which will be conducted as established by Wiebe et al. in their RCT for mesial temporal lobe epilepsy [4]. Two experienced neurosurgeons will perform ATL for mTLE and resection will be 5.5 cm on the non-dominant hemisphere or 4.5 cm on the dominant hemisphere, as referenced in Wiebe et al. [4]. The mesial part of the resection will include the ipsilateral amygdala, hippocampus, and uncinate gyrus. The full procedure will be recorded by the neurosurgeons performing the resection. Patients will continue taking the same AEDs that they had been taking prior to surgery under the supervision of a neurologist. Patients will not stop AED treatment until the 1-year follow-up even if they do not experience seizures.

Patients enrolled in arm 2 will undergo SEEG implantation and RF-TC for mTLE. SEEG implantation will be performed following pre-surgical evaluation. The target points of the SEEG electrodes will cover the mesial part of the ipsilateral temporal region. Both long-axis and parallel vertical depth electrodes generating a 3-dimensional space will be designed to guide RF-TC in cases of small ablation volume (Fig. 2). For each patient, bipolar coagulation will be performed on each of two contiguous contacts of the longitudinal and vertical electrodes using the same parameters. Contacts between electrodes will be further coagulated at intervals of < 5 mm to ensure freedom from vascular injury. This modified approach provides extended volume including the amygdala, hippocampus, subiculum, and part of the entorhinal cortex (Fig. 2). Similarly, patients will not stop taking AEDs until the 1-year follow-up.

**Fig. 2 Fig2:**
[figure not shown]
**A**, **B** The distribution of SEEG electrodes via three-dimensional reconstruction and the relationship between electrodes and the mesial temporal area. OH, T, TH, and TB were implanted in the hippocampus. TA was implanted in the amygdala. **C** The combination of preoperative T1-weighted images and postoperative CT images. The relative anatomical position of the SEEG electrodes and brain structure can be observed. **D** Postoperative T2-weighted MRIs obtained within 1 week of SEEG-guided RF-TC

Two doctors will store and manage the data entered in this study ([name] and [name]). If participants withdraw from this RCT, all the information will not be stored except the basic identity and consent form (information prior to the withdrawal).

### Outcomes

The primary outcome measure is cognitive function after treatment, which will be assessed using the Chinese version of the full-scale Wechsler Adult Intelligence Scale-IV (WAIS-IV-C) for adults (> 16 years old) or the Chinese version of the Wechsler Children’s Intelligence Scale-IV (WCIS-IV-C) for children. Assessments will be performed before and 1 year after surgery. Higher values are considered indicative of better outcomes.

Secondary outcomes are as follows:
Post-surgical seizure outcomes after 1 year based on Engel classification. Engel 1A and 1B will be considered to reflect seizure freedom, while Engel 1C–4 will be considered to reflect seizure recurrence. Seizure outcomes will be assessed at 3, 6, and 12 months via telephone interviews or outpatient visits with the patient and direct relatives. Seizures occurring within the first 2 weeks after surgery will not be considered to reflect seizure recurrence.Visual field examination results: We will compare the number of patients with visual field defects between arm 1 and arm 2 before and 1 year after surgery.The number of participants with procedure-related complications 1 year after surgery, including postoperative stroke with or without symptoms (via MRI), postoperative intracranial bleeding with or without symptoms (via MRI), postoperative intracranial infection, postoperative wound infection, and postoperative subcutaneous dropsy.Quality of life after treatment. Values will be assessed using the Quality of Life in Epilepsy-89 scale (QOLIE-89) for adults (age 17–60) and the Quality of Life in Epilepsy-48 scale (QOLIE-48) for children (age 14–16) 1 year after surgery.Average hospitalisation expenses 1 month after surgery.

All clinical and outcome-related data will be collected by two experienced clinicians (one neurologist and one neurosurgeon). Detailed data collection and follow-up timeline are shown in Table 1. For each patient, a case report form (CRF) including comprehensive patient information, clinical data, scale results, and outcomes will be completed.

**Table 1 Tab1:** Data collection

Assessment	Baseline	Follow-up 7 ± 2 days	Follow-up 90 ± 7 days	Follow-up 180 ± 7 days	Follow-up 360 ± 14 days
Informed consent	□				
Demographics	□				
History of epilepsy	□				
Physical examination	□	□			□
EEG	□		*□		□
AEDs	□	□	□	□	□
Visual field assessment	□				□
WAIS-IV-C/WCIS-IV-C	□				□
QOLIE-89/QOLIE-48	□				□
Engel classification		□	□	□	□
PET	□				
MRI	□	□	*□		□
Adverse events		□	□	□	□
Concomitant medication	□	□	□	□	□

□, required; *□, optional; *EEG*, electroencephalogram; *AEDs*, antiepileptic drugs; *WAIS-IV-C*, Chinese version of the Wechsler Adult Intelligence Scale-IV; *WCIS-IV-C*, Chinese version of the Wechsler Children’s Intelligence Scale-IV; *QOLIE-89*, Quality of Life in Epilepsy-89; *QOLIE-48*, Quality of Life in Epilepsy-48; *PET*, positron emission tomography; *MRI*, magnetic resonance imaging

### Sample size

The sample size was calculated based on our previous experience (cognitive performance decrease of 25% after ATL), similar to findings reported in earlier studies [18]. Approximately 5% of patients exhibited decreased cognitive performance after SEEG-guided RF-TC in our previous series, while most previous studies have reported improvements or a lack of impairment [20–22]. We expect to enrol 20 patients in each arm using a one-sided 95% confidence interval, a non-inferiority limit of 10%, and an expected withdraw rate of 20%. Thus, we aim to include a total of 40 patients in this trial. Patients will be recruited from outpatient and MDT with strict inclusion criteria.

Participants will be replaced if they withdraw at any time prior to the final follow-up supervised by [name] and [name]. Those who withdraw from the study during treatment because of specific medical or technical events will also be monitored and replaced. The trial conduct will be audited by the investigators with the whole MDT monthly.

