### Randomisation and blinding

All patients and their direct relatives will be informed regarding the intentions and technological procedures involved in the study at the time of hospitalisation. Written informed consent will be obtained following patient agreement. The sealed envelope system will be used for randomisation of the patients into two groups. The envelope will be supported by a recognised third-party organisation. Neither the investigator nor the participants will be aware of each envelope’s contents.

Clinicians will know the exact allocation of each patient, and blinding will not be performed. In addition, patients will not be blinded due to the differences between the treatment strategies. Patients will also provide written informed consent the day prior to surgery.

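### Replacing participants who withdraw and not storing their data leaves completers plus replacements instead of the randomised groups, with possible bias in either direction

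*Protocol article*

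**What the plan says.** Three statements in the protocol article bear on this.

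- Sample size: "Participants will be replaced if they withdraw at any time prior to the final follow-up". The next sentence reads: "Those who withdraw from the study during treatment because of specific medical or technical events will also be monitored and replaced".
- Interventions, in the data-handling paragraph after Fig. 2: "If participants withdraw from this RCT, all the information will not be stored except the basic identity and consent form (information prior to the withdrawal", where the parenthesis then closes. It is unclear whether the parenthesis describes what is kept or what is not stored. The main clause excludes everything but identity and consent form.
- Sample size again: the inputs include "an expected withdraw rate of 20" per cent, and the section concludes "Thus, we aim to include a total of 40 patients in this trial".

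The surrounding design matters too. Outcomes places the Wechsler assessment before surgery and at 1 year only. Randomisation and blinding says that neither clinicians nor patients are blinded. Statistical analysis names no analysis set that would retain withdrawn patients.

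**The concern.** Replacement after randomisation changes who is compared. The final groups are no longer those that chance formed: they are the patients who stayed, plus later entrants. Because the primary outcome is measured once after surgery, any withdrawal within the year removes it.

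The non-storage rule makes this hard to repair. A later analysis plan can define an intention-to-treat set, but it cannot analyse records that the protocol says are not held. A patient with a postoperative bleed or a failed procedure who then withdraws could be replaced and be absent from the complication count and the seizure outcome.

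Outcome-related withdrawal is plausible. The trial is open label, and only the RF-TC arm has electrode implantation, monitoring to a first seizure and then coagulation, so exits for technical reasons may not fall equally on both arms. The documents give no data on this. The plan aims at a non-inferiority conclusion, for which selective loss in one arm can matter a great deal.

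**Working it through.** **1. Is the 20 per arm already inflated?**

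Inputs from Sample size: decline 25% after ATL and about 5% after RF-TC, margin 10%, one-sided 5% ("using a one-sided 95% confidence interval"), withdrawal 20%. Two assumptions are added: 25% is a proportion of patients (the wording is ambiguous), and power is 80% (not stated).

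- Variance term: 0.25 × 0.75 + 0.05 × 0.95 = 0.1875 + 0.0475 = 0.235.
- Distance from the margin: (0.25 − 0.05) + 0.10 = 0.30.
- n per arm = 0.235 × (1.645 + 0.842)² / 0.30² = 16.14.
- With 20% withdrawal: 16.14 / 0.8 = 20.2.

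This reproduces the stated 20. Rounding up at each step gives 17 and then 22, so the match is within 2 patients per arm. At 85% or 90% power the same method gives 24 or 29 per arm, which does not match.

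**2. Is replacement needed?**

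Power = Φ(0.30 / √(0.235/n) − 1.645).

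- n = 16: 0.30 / 0.1212 − 1.645 = 0.83, power 79.7%.
- n = 20: 0.30 / 0.1084 − 1.645 = 1.12, power 86.9%.

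So 40 randomised with 20% lost already gives about 80% on these inputs. If instead 20 completers per arm are required, 20 / 0.8 = 25 must be randomised per arm, 50 in all, and about 10 of them would be removed with their data. The article does not say which is meant. The normal approximation is rough here, with 16 × 0.05 = 0.8 expected RF-TC events.

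**3. What could selective withdrawal do?**

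Let p be the true decline rate, 20% the overall withdrawal, and r the ratio of withdrawal in decliners to that in others. Then w₀ = 0.2 / (pr + 1 − p), w₁ = r·w₀, and the rate among completers is p(1 − w₁) / 0.8.

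| r | true 25% seen as | true 5% seen as | true 35% seen as |
|---|---|---|---|
| 1 | 25.0% | 5.0% | 35.0% |
| 2 | 21.2% | 3.9% | 30.8% |
| 3 | 18.7% | 2.8% | 28.3% |
| 4 | 17.0% | 1.9% | 26.7% |

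*Selective loss from RF-TC only.* Put RF-TC truly at the margin (35% v 25%), with 20 completers per arm and a Wald interval. The chance of wrongly declaring non-inferiority is 5.9%, 10.1%, 13.6% and 16.3% for r = 1, 2, 3 and 4. The 5.9% at r = 1 is the small-sample error of the interval, not bias.

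*Selective loss from ATL only.* With true rates of 25% and 5% and r = 4, ATL is seen as 17.0%. By exact enumeration with the same interval, power falls from about 90% to 78%, so the bias runs against non-inferiority.

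*Equal dependence in both arms.* At r = 4 the observed difference is 17.0 − 1.9 = 15.1 points instead of 20.

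**The case against.** The strongest reply is that the bias is hypothetical. Nothing in the article shows that withdrawal depends on outcome or differs by arm, and without that dependence replacement causes no bias. This stands: the error rates above are an illustration, and selective loss from ATL would work against RF-TC.

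It can also be said that patients who leave for medical or technical reasons are to be monitored, that a case report form is planned for each patient, and that adverse events are scheduled from day 7. This softens the point on harms, so one can say only that such events can drop out, not that they must. But no sentence says that these data are kept or analysed after withdrawal. Clinical monitoring and non-storage of research data need not contradict each other.

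A third reply is that IQ before 1 year is never measured, so keeping data to the point of withdrawal would not restore the primary outcome. That is correct, and it is why continued follow-up has to be part of the remedy.

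A reader might infer more than the text supports:

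- **Consent as an exit.** The protocol says "Patients will also provide written informed consent the day prior to surgery". It does not place this clearly after randomisation or present it as a second decision point on taking part.
- **Known allocation of replacements.** The article does not say how a replacement is allocated, and it describes third-party sealed envelopes. Choice of arm by hand is not shown.
- **Two lost complications equal the margin.** One patient in 20 is 5 points, so two make 10. But the 10% limit is set beside cognitive rates only, and complications are to be compared qualitatively. At the planned 5%, RF-TC would expect just one decliner in 20.

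**Conclusion.** The point holds as a fault in two written rules, not as an omission that an analysis plan might fill. Applied together, they leave completers plus replacements, remove the means of recovering an intention-to-treat set, and allow failures and harms followed by withdrawal to leave the results. It should be corrected before analysis.

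The size of any bias is unknown. It is zero if withdrawal is unrelated to outcome. False non-inferiority of about 10% to 16% arises only under the stated illustration: 20% withdrawal, RF-TC truly at the margin, and decliners leaving RF-TC alone 2 to 4 times as often. It would be wrong to infer that the rules necessarily favour RF-TC.

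That attrition appears to be allowed for twice is a lesser matter of clarity. It rests on reading 25% as a proportion of patients and on 80% power. On those inputs, power is about 80% or higher either way.

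**What to change.** Delete the two replacement sentences in Sample size and the non-storage sentence in Interventions. State instead that:

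- every randomised patient is analysed in the assigned arm;
- stopping the assigned treatment is not withdrawal from follow-up;
- data collected up to withdrawal are kept, within the limits of consent;
- adverse-event, Engel and IQ follow-up continues unless the patient refuses;
- the 20% inflation is the only allowance for attrition.

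For anyone already replaced, restore the original patient to the analysis where data and consent allow, and report the number, arm, timing and reason.

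The cost is a protocol amendment and possibly renewed consent from patients enrolled under the non-storage rule; the consent documents are not shown. Evaluable numbers per arm may be slightly lower than with replacement, but no extra patients are needed. Trial status gives an approximate recruitment end of February 2021, before the article appeared, so the change may come after some replacements. Disclosure would still be possible then, but records already deleted could not be recovered.
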